## Abstract

**Objective:**

Ovarian cancer is the fifth cause of cancer-related death among women. The benefit of targeted therapy for ovarian cancer patients is limited even if treatment is stratified by molecular signature. There remains a high unmet need for alternative diagnostics that better predict targeted therapy, as current diagnostics are generally inaccurate predictors. Quantitative assessment of functional signal transduction pathway (STP) activity from mRNA measurements of target genes is an alternative approach. Therefore, we aim to identify aberrantly activated STPs in tumour tissue of patients with recurrent ovarian cancer and start *phenotype*-guided targeted therapy to improve survival without compromising quality of life.

**Study design:**

Patients with recurrent ovarian cancer and either 1) have platinum-resistant disease, 2) refrain from standard therapy or 3) are asymptomatic and not yet eligible for standard therapy will be included in this multi-centre prospective cohort study with multiple stepwise executed treatment arms. Targeted therapy will be available for patients with aberrantly high functional activity of the oestrogen receptor, androgen receptor, phosphoinositide 3-kinase or Hedgehog STP. The primary endpoint of this study is the progression-free survival (PFS) ratio (PFS2/PFS1 ratio) according to RECIST 1.1 determined by the PFS on matched targeted therapy (PFS2) compared to PFS on prior therapy (PFS1). Secondary endpoints include among others best overall response, overall survival, side effects, health-related quality of life and cost-effectiveness.

**Conclusion:**

The results of this study will show the clinical applicability of STP activity in selecting recurrent ovarian cancer patients for effective therapies.

**Trial registration number**: NL2020-005091-36 (EudraCT) and NCT03458221 (ClinicalTrials.gov).

## Introduction

1

Ovarian cancer is the fifth leading cause of cancer death among women in the Western world [1]. The majority of the patients is diagnosed with advanced stage disease, which requires extensive cytoreductive surgery in combination with platinum and paclitaxel containing chemotherapy [2]. Despite this extensive treatment, recurrent disease almost invariably occurs resulting in a five-year survival rate ranging between 20% and 41% [3], which has not changed significantly over the last decades [4]. Recurrent ovarian cancer could be treated with second-/third-line chemotherapy and targeted therapies, such as poly(ADP-ribose) polymerase (PARP) inhibitors [2]. Although other targeted therapy options are rapidly expanding [5], response rates often fall short of expectations [6]. This can be the result of suboptimal selection based on inadequate molecular diagnostics. Therefore, there is an urgent need to improve patient stratification methods to allocate patients with ovarian cancer to effective targeted therapies and prevent unnecessary side effects of ineffective therapies.

Tumour cell proliferation, differentiation and migration is often driven by aberrant cellular activity of signal transduction pathways (STPs) [7]. STPs can be categorized as nuclear receptor pathways (e.g. oestrogen receptor (ER) and androgen receptor (AR)), developmental pathways (e.g. Hedgehog (HH), transforming growth factor beta (TGF-β), Notch), and highly complex growth factor regulated pathways (e.g. phosphoinositide 3-kinase (PI3K) and mitogen-activated protein kinase (MAPK)). During the past decades, our knowledge on the complex mechanisms of action of these STPs has expanded and studies demonstrated associations between aberrant STP activity and ovarian carcinogenesis [[8], [9], [10], [11], [12], [13], [14]].

The introduction of whole genome sequencing technologies enabled the identification of genomic alterations associated with these STPs in tumour samples. Unfortunately, the implementation of genomic-based targeted therapy has not been as successful as initially expected [15]. Although a proportion of patients in molecular profiling studies demonstrates clinical benefit, the majority of these carefully selected patients lack response to costly targeted drugs [16,17]. These findings suggest that we have overestimated the contribution of the cancers’ *genotype* in predicting therapy response, but it could be questioned if the sole presence of gene alterations (e.g. gene mutations or amplifications) is sufficient to provide information on the functional activation status of STPs. Until now, the *functional phenotype* of tumour cells that is influenced by other factors, such as the tumour microenvironment is often disregarded.

In recognition of the significance of the cancer's *phenotype*, an alternative approach to assess STP activity was developed using Bayesian computational network models [[18], [19], [20], [21], [22], [23]]. The models infer STP activity from mRNA measurements of well-validated direct target genes of the transcription factor complex associated with the respective STP from paraffin-embedded tumour samples. Until now, models have been developed for the ER, AR, HH, TGF-β, Notch, PI3K, and MAPK pathways. While current approaches focus on a single molecular trait, these models use expression levels of several pathway-specific target genes and are therefore thought to be a more precise way to interpret functional STP activity. Previous studies including other tumour types, such as breast and salivary duct cancer, suggested the mRNA-based assay to be of value in the selection of patients for targeted therapy based on activated STPs [[24], [25], [26]].

Our research group investigated STP activity in several subtypes of ovarian cancer to identify which STPs could be potential targets for personalized medicine [27,28]. Furthermore, we determined STP activity in morphologically normal Fallopian tube epithelium (FTE) of healthy women, the considered tissue of origin of most high-grade serous carcinoma (HGSC), to establish normal STP activity as a reference. [29] In the current study, we aim to determine actionable tumour-promoting STPs in tumour samples of recurrent ovarian cancer patients based on these results and implement *phenotype*-guided targeted therapy to improve survival without compromising quality of life. Therefore, we propose a prospective, parallel-group cohort study involving patients with recurrent ovarian cancer to be treated with approved targeted drugs, if identified with an aberrantly activated STP.

## Methods

2

### Study design

2.1

The Signal TrAnsduction Pathway activity analysis for OVarian cancER treatment (STAPOVER) study is an investigator-initiated, multi-centre, prospective, parallel-group cohort study with stepwise executed treatment arms. Patients with platinum-resistant recurrent ovarian cancer, patients with recurrent ovarian cancer who refrain from standard therapy and patients with recurrent ovarian cancer who are not yet eligible for standard palliative chemotherapy due to asymptomatic disease, will be included to receive targeted therapy based on aberrantly active STPs, identified by the STP activity assay. Patients diagnosed with any histological subtype of ovarian cancer are eligible for inclusion in the study. The rationale for including all histological subtypes is driven by the need to move beyond histological classifications and focus on molecular profiling. In the individual treatment arms, a modified version (three-stage) of Simon's two-stage design is incorporated (Fig. 1) [30].

**Fig. 1 fig1:**
[figure not shown]
Flowchart displaying the three-stage design for inclusion of patients per treatment arm. PFS; progression-free survival.

### Eligibility criteria

2.2

Adult women (age ≥18 years) diagnosed with recurrent ovarian cancer of any histological subtype who either 1) have platinum-resistant disease, defined as disease recurrence or progression within six months of last platinum-based chemotherapy (e.g. cisplatin or carboplatin) 2) refrain from standard therapy or 3) are asymptomatic and not yet eligible for standard therapy with an increased CA125 tumour marker of a nadir above 35 U/ml for at least 28 days, are eligible for enrolment when the following inclusion criteria are met.•Progressive disease after at least one prior line of systemic treatment for recurrent disease.•Radiologically evaluable disease according to RECIST 1.1 [31].•Ability and willingness to provide a tumour biopsy after the last course of standard treatment and before start of the study.•Ability and willingness to provide written and oral consent.•Able to speak and understand the Dutch language.•WHO performance status 0-II.•Adequate renal and liver function to start matched targeted therapy (according to the local clinician).•Adequate use of contraceptives in case of patients with childbearing potential.

Women are not eligible to participate in the study in case any of the following exclusion criteria are met.•Patient is receiving any other anti-cancer therapy or is chemotherapy naïve. The required wash-out period prior to the start of matched targeted therapy is at least three weeks.•Patient is diagnosed with or treated for a second primary tumour (except non-melanoma skin tumour) one year prior to study inclusion.•Inability to obtain (sufficient) tumour material.•Previous use of the selected targeted drug as anti-cancer agent.•Pregnant or lactating women.•Simultaneous participation in another treatment-related clinical trial.•Patients with any other clinically significant medical condition which, in the opinion of the local clinician, makes it undesirable for the patient to participate in this study or which could jeopardize compliance with study requirements.

### Study procedures

2.3

Informed consent will be obtained from the patients who are willing to participate and meeting the inclusion criteria. Subsequently, one histological biopsy will be collected to obtain tumour tissue for the STP activity assay. Patients are eligible for treatment with matched targeted therapy if an aberrantly activated STP is observed. Women with high activity of the ER, AR, PI3K or HH pathway will be included for treatment with either letrozole (arm A), bicalutamide (arm B), or itraconazole (arm C and D) (Fig. 2). These targeted drugs have been studied in ovarian cancer patients with acceptable side effects [[32], [33], [34], [35], [36], [37], [38], [39], [40], [41], [42]]. Patients who are not eligible to participate in the study will continue to receive standard of care by choice of the treating clinician. These patients are asked for consent to remain on study to complete questionnaires at baseline, every 12 weeks during the next course of treatment and 12 weeks after the end of treatment. Questionnaires are used for secondary analyses, such as side effects, quality of life and cost-effectiveness.

**Fig. 2 fig2:**
[figure not shown]
Flowchart of the study design. STP; signal transduction pathway, ER; oestrogen receptor, AR; androgen receptor, HH; Hedgehog, PI3K; phosphoinositide 3-kinase, TGF-β; transforming growth factor beta, MAPK; mitogen activated protein kinase.

### Tumour sampling

2.4

Tumour tissue will be obtained from at least one tumour site through a biopsy guided by ultrasound or CT-scan, or through a (pre-planned) cytoreductive surgical procedure. In case of multiple tumour sites, a tumour site based on accessibility and safety risks will be selected. Successfully obtained tumour tissue will be formalin-fixed paraffin-embedded (FFPE) by the hospital's histopathological laboratory. In case biopsy fails, e.g. because of insufficient tumour tissue or no accessible tumour site, the patient will be excluded from the study.

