### Pre-treatment evaluation before start of matched targeted therapy

2.9

Before the start of the recommended matched targeted therapy, patients will undergo a pre-treatment evaluation by their treating clinician. Baseline characteristics will be registered in the electronic case report form (eCRF). Furthermore, physical examination will be performed and the treating clinician will determine if any safety concerns exist. The treating clinician will assess if the patient has adequate renal and kidney function and checks for interactions between the matched targeted therapy and concomitant medication. Imaging of the tumour and evaluation by RECIST 1.1 of the tumour will be performed at baseline [31].

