### Plan of analysis

3.3

The proportion of patients who achieved a PFS2/PFS1 ratio ≥ 1.3 will be calculated from the total of patients that received matched targeted therapy. The primary endpoint will be tested by a one-sided exact test. Since histological subtype is a prognostic factor for PFS [36], subgroup analysis will be performed in case of adequate numbers.

Planned statistical analysis for the secondary outcome measures include the Kaplan-Meier survival curves tested with log-rank tests and Cox proportional hazard models for survival analysis. Furthermore, the predictive value of STP activity assay will be determined by correlations between STP activity scores and PFS2 using the Pearson or Spearman correlation coefficient. If patients undergo a voluntary second post-treatment biopsy, change in STP activity score will be calculated for each respective STP compared to the STP scores from the pre-treatment biopsy.

Using the appropriate algorithms, the side effects and health-related quality of life questionnaires will be analysed and compared accordingly between the group of patients that received matched targeted therapy and patients that received standard therapy. Together with the PFS, these results will be used in a quality adjusted life year calculation in order to calculate the cost-effectiveness and cost-utility ratios of matched targeted therapy. In addition, subgroup analysis per treatment arm will be conducted.

Descriptive statistics will be used to describe patient characteristics. Categorical variables will be expressed as a number with the percentage of the total study group. The chi-squared test or Fisher's exact test will be used to analyse associations between categorical variables. Continuous variables will be presented as mean with standard deviation or as median with interquartile range, whenever appropriate. A *t*-test or Mann-Whitney *U* test will be used to analyse associations between continuous variables.

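### Study tissue may come from cytoreductive surgery performed between the two periods that the PFS ratio compares, and the primary analysis does not separate those patients

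*Protocol article*

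**What the plan says.** All references are to the protocol article.

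- **Route of sampling (2.4).** Tissue is obtained "through a biopsy guided by ultrasound or CT-scan, or through a (pre-planned) cytoreductive surgical procedure".
- **Timing (2.2).** The inclusion criterion reads "Ability and willingness to provide a tumour biopsy after the last course of standard treatment and before start of the study".
- **Order (2.3).** Consent is taken from patients who meet the inclusion criteria. "Subsequently, one histological biopsy will be collected to obtain tumour tissue for the STP activity assay".
- **State at entry (2.2).** Two of those criteria are "Progressive disease after at least one prior line of systemic treatment for recurrent disease" and "Radiologically evaluable disease according to RECIST 1.1".
- **Wash-out (2.2).** "The required wash-out period prior to the start of matched targeted therapy is at least three weeks". Surgery is not mentioned.
- **Baseline (2.9).** "Imaging of the tumour and evaluation by RECIST 1.1 of the tumour will be performed at baseline". No consequence is given if evaluable disease is no longer present.
- **Endpoint (3.1).** PFS1 belongs to the therapy given immediately before enrolment, PFS2 to the matched therapy.
- **Analysis set (3.3).** The proportion with a ratio of at least 1.3 "will be calculated from the total of patients that received matched targeted therapy".

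**The concern.** Cytoreductive surgery acts on the tumour. If it takes place after PFS1 has ended and before the matched drug starts, any delay in progression that it causes falls into PFS2 and is credited to the drug. Section 3.2 justifies the ratio by letting each patient be her own control. That deals with stable characteristics such as histology, but not with an intervention placed between the two periods. The arms have no concurrent randomised control that would share the effect, and a wash-out interval does not reverse removal of tumour.

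A second effect may run the other way. A patient whose evaluable disease has been resected cannot show response by shrinkage, while her progression has to come from new or regrown lesions. The primary ratio and best overall response could then be distorted in opposite directions in the same patient.

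What is at stake is whether a positive arm can be read as activity of the matched drug.

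**Working it through.** **Step 1: where the surgery falls.** Progressive disease is an entry criterion (2.2), so PFS1 has ended before consent. Tissue follows consent (2.3), and must be taken after the last standard treatment and before study start (2.2). Surgery used as the sampling route (2.4) therefore lies between the PFS1 progression and the first dose. The article does not give an explicit start date for PFS2, but the problem is the same whether the clock starts at enrolment or at first dose.

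**Step 2: whether another rule deals with it.** The wash-out rule does not mention surgery. Section 3.2 replaces only patients who withdraw before matched therapy. Section 3.3 takes all treated patients. Nothing excludes surgically sampled patients or analyses them separately.

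**Step 3: reproduce the planned sample size.** Section 3.2 gives a null of 15%, 80% power, one-sided 0.10 and 37 patients per arm. The trial's own alternative is not stated; 30% is one of the two values it cites. In an exact single-stage binomial design the smallest adequate n is 37, with success at 9 or more:

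- P(X ≥ 9 | 37, 0.15) = 0.0924
- P(X ≥ 9 | 37, 0.30) = 0.8237

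With the other cited value, 24%, the smallest n would be 87. So 37 is the exact design for 15% against 30%, and the 9-of-37 rule is inferred from it. The room below the nominal level is 0.10 − 0.0924 = 0.0076.

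**Step 4: illustrate the size.** Let f be the share of treated patients sampled by cytoreductive surgery, and q their chance of a ratio of at least 1.3 when the drug is inert. The article gives neither, so both are assumptions. Then

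p = 0.15 + f × (q − 0.15), and the false-positive rate is P(X ≥ 9 | 37, p).

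For example, f = 0.05 and q = 0.40 give p = 0.15 + 0.05 × 0.25 = 0.1625 and a rate of 0.135.

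| f | q = 0.20 | q = 0.40 | q = 0.60 |
|---|---|---|---|
| 0 | 0.092 | 0.092 | 0.092 |
| 2% | 0.095 | 0.108 | 0.122 |
| 5% | 0.100 | 0.135 | 0.176 |
| 10% | 0.108 | 0.187 | 0.287 |

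These figures treat the final test as single-stage. The interim rules use a ratio of 1.0 rather than 1.3; they can only close arms, so they would lower the rates somewhat.

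**Step 5: evaluable disease.** Section 2.2 requires it at entry. Section 2.9 takes a RECIST baseline before the drug and so would reveal its loss, but does not say whether the patient still qualifies.

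**The case against.** The strongest case against is that the size is speculative. Image-guided biopsy is named first, surgery is an alternative, and section 2.3 speaks of a single biopsy. The entry groups are platinum-resistant patients, patients who decline standard therapy and asymptomatic patients. Nothing suggests that surgical sampling is common. At a 2% share with 20-40% success after surgery, the rate is only 0.095-0.108 against 0.092. This stands, and it limits what can be claimed.

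Three stronger readings are tempting and are not supported:

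- **A grossly inflated error rate.** A 20% surgical share with 40-60% success would give 0.31-0.54, but the article supports neither input.
- **PFS1 always on systemic treatment alone.** Section 3.1 does not say that the prior line was free of surgery. If it also included cytoreduction, the asymmetry shrinks or could reverse.
- **Evaluable disease will be gone.** It may be. The baseline scan, the tumour board decision and the target of 37 evaluable patients could each stop such a patient from counting; none is stated as a rule for this case.

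It can also be said that handling an intervening procedure belongs in the full protocol or analysis plan, which are not shown. That holds for a sensitivity analysis as such. But the article itself fixes the sampling route, the timing, the ratio and the all-treated denominator, and it is their combination that creates the problem.

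Finally, removing treated patients from the primary set and replacing them would conflict with sections 3.2 and 3.3. On the article's own yield it would cost about 366 / 148 = 2.5 biopsies per replacement. That objection is accepted, and the fix below does not require it.

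**Conclusion.** The point holds as a confounding route that the plan permits and does not address. Followed as written, the plan credits to the matched drug any effect on PFS2 of cytoreductive surgery done for sampling.

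Its size cannot be determined from the article. In the illustration the false-positive rate ranges from close to the planned 0.092, if surgical sampling is very rare and surgery has little effect, to 0.287 at a 10% share with 60% success. With under 0.01 to spare below 0.10, a few surgical patients per arm can be enough to exceed the nominal level. This rests on the inferred 9-of-37 rule, an inert drug, and assumed values for both the surgical share and success after surgery. Loss of evaluable disease is a possibility with no stated consequence, not an established defect.

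**What to change.** 1. In sections 2.2 and 2.9, state that radiologically evaluable disease is judged on the baseline scan taken after the tissue procedure.
2. Record the sampling route for every patient. In section 3.3, keep the all-treated primary proportion and prespecify, per arm, a sensitivity analysis of that proportion and of best overall response. It leaves out patients who had cytoreductive surgery between PFS1 progression and the start of matched therapy. Report those patients separately.
3. State that success will not be claimed for an arm on the all-treated result without showing this analysis beside it.

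Surgical tissue stays in the assay and in the proportion with an actionable pathway. No rule on surgery itself is proposed.

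The cost is a few sentences and one data field. A few patients may no longer qualify on the post-procedure scan. The sensitivity analysis loses some precision: with two surgical patients left out, 37 − 2 = 35 remain, the exact cut-off is still 9 (P(X ≥ 9 | 35, 0.15) = 0.069), and power at 30% falls from 0.824 to P(X ≥ 9 | 35, 0.30) = 0.766.

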### Preparation of tumour samples

2.5

In addition to standard diagnostics, for the STAPOVER study at least 20 sections of 5 μ m will be cut from the FFPE sample with a microtome. The first and last study slide will be haematoxylin and eosin (H&E) stained. The H&E-stained slide will be revised by a local pathologist to annotate a tumour area containing the highest amount of tumour cell nuclei (≥50 %).

The coordinating centre will provide a study number for each individual patient to label the study slides before they will be transported to InnoSIGN for STP activity assay. The remainder of the FFPE samples and slides for standard diagnostics will be archived in the participating centre. If sufficient study slides have been obtained, several slides will be archived by the coordinating centre for optional analysis (such as immunohistochemical biomarker analysis and DNA/RNA sequencing).

### STP activity assay and determination of high STP activity

2.6

Using the annotated H&E slide as reference, tumour cells will be manually scraped off the study slides for the STP activity assay. Next, mRNA will be isolated from the tumour cells using the RNeasy FFPE Kit (Qiagen). Expression levels of pathway-specific target genes will be measured with real-time quantitative reverse transcription-PCR (RT-qPCR) analysis using the SuperScript III Platinum One-Step qRT-PCR Kit (Thermo Fisher Scientific) and commercially available OncoSIGNal 96-wells PCR plates (InnoSIGN). An internal quality control of reference genes is performed to confirm sufficient mRNA input for the assay.

STP activity assay provides a functional pathway activity score defined on a scale from 0 to 100, where the measured range of pathway activity may vary with the analysed tissue type. A score of 0 corresponds with the lowest odds of an active pathway and conversely 100 corresponds with the highest odds. In a prior study, we quantified the activity of STPs in epithelial cells derived from morphologically normal Fallopian tubes[29]. This analysis served as a basis to establish the reference levels for normal STP activity. We defined cut-off values for high STP activity in tumour samples, which were determined as two standard deviations above the mean value of STP activity measured in FTE samples. Individual STP activity assay results will be presented and analysed in a graph as shown in Fig. 3. This format contains the STP activity distributions measured in previous cohorts of normal FTE (blue curve), HGSC samples (red curve) and low-grade serous ovarian carcinoma (LGSC) samples (purple curve) [28,29,43]. For each measured STP, data is displayed in a single graph. The black dotted line represents the cut-off value for high STP activity. Before the start of the study, cut-off values will be updated to values in which the most recent results of the STP activity of the normal FTE are included. The individual STP activity measured in the patient's tumour sample will be plotted in the format. In case the individual STP activity transcends the cut-off (black dotted line), the STP will be classified as aberrantly activated. STP activity results will be sent to the principal investigators, who share the results with the multidisciplinary tumour board (MTB).

